### **Secondary objectives**

To assess the immunogenicity and correlates of efficacy of a heterologous prime -boost vaccine strategy with ChAd63 ME-TRAP and MVA ME-TRAP in healthy adults in Senegal.

To assess the safety and reactogenicity of a heterologous prime -boost vaccine strategy with ChAd63 ME-TRAP and MVA ME-TRAP in healthy adults in Senegal.

To assess the impact of natural immunity (cellular and humoral) on time to re-infection in healthy adults in Senegal

### **Tertiary objective**

To assess the efficacy of a heterologous prime -boost vaccine strategy with ChAd63 ME-TRAP and MVA ME- TRAP in a larger sample of healthy adults living in malaria-endemic regions of Africa by undertaking a metaanalysis combining the results of the proposed study with those of the parallel study, VAC046.

## **Methodology**

This is a single blinded randomised vaccine trial. The primary focus of the research will be directed at the impact of the proposed vaccine on the numbers of parasite carriers over a 2 month period following vaccination. This period will occur during the 2012 malaria transmission season.

## **Sensitization and recruitment**

The local administrative and community leaders as well as health care workers will be the first to be sensitized about the study. Public meetings will be arranged to inform the communities of the planned study.

During a meeting the investigators will explain the following: the need for a vaccine, the current status of vaccine development, the study screening and informed consent procedure; risks of vaccination and the possible benefits of vaccination. After this meeting field workers will identify potential volunteers, and information sheets translated into relevant local languages will be distributed. The field workers will conduct individual meetings with the participants to ensure understanding of the information sheet and consent form. Individuals who feel that the trial is appropriate for them will be invited to attend a formal screening visit in the study dispensaries. Further discussion will then occur with volunteers in the study dispensaries where the study clinicians will seek informed consent with an experienced field worker.

After consent is obtained, each consented volunteer will be screened for clinically significant acute or chronic disease, using both general physical examination and screening laboratory tests (full blood count (FBC), Hepatitis B, alanine transaminase (ALT) and creatinine. The findings at screening will be used to determine whether or not the volunteer is eligible to participate in the trial. Volunteers eligible to participate in the trial will meet all of the inclusion criteria and none of the exclusion criteria (listed below). Likelihood of migration will be an important factor in determining eligibility to participate in the trial. All volunteers will be informed of results of laboratory tests and referral to an appropriate health facility done where necessary. Volunteers will be informed of the need to conduct anonymous HIV testing. All volunteers will receive pre-test counselling from a trained counsellor who will also do post-test counselling after giving the results. HIV positivity will be an exclusion criterion. In order to maintain the confidentiality of those volunteers infected with HIV, we will make it clear that during screening one can be excluded due to a range of diseases (not just HIV) as well as abnormal laboratory results. Enrolment (receipt of first vaccination) will be done within 90 days of screening. Volunteers enrolled will be given photo identity (ID) cards for ease of identification and also to serve as a reminder of the appointment dates. These will be destroyed at the end of the study.

Vaccination, observation and blood sampling will occur at King Baudouin hospital.

## **Study groups**

Subjects will be randomized to receive either ChAd63 ME-TRAP and MVA ME-TRAP or control vaccination with Rabies vaccine. To preserve blinding, Rabies vaccine will be administered in a 0, 2 month schedule. This differs from the standard schedule for rabies vaccination, however, administration of rabies vaccine by alternative schedules may still provide some protective efficacy against rabies. In addition, all participants will be offered a standard schedule of Rabies vaccine after the trial comes to an end.

Simple randomisation into the study groups will be done by an independent statistician and the study clinicians with an allocation ratio of 1:1 to study groups taking into account their area of residence. A randomization code list will be generated by an independent statistician and its use guided by a clear standard operating procedure (SOP). Allocation concealment will be employed by use of opaque sealed envelopes. The volunteers, fieldworkers and laboratory scientists will be blinded to vaccine allocation until the end of the study, but the clinical investigators will not be blinded.

All vaccinations will be administered by the intramuscular route – IM. Randomization into groups will be as follows:

- **Group 1**(60 volunteers): ChAd63 ME-TRAP  $5 \times 10^{10}$  viral particles (vp) followed by MVA ME-TRAP  $2 \times 10^8$  plaque forming units (pfu) 8 weeks later.
- **Group 2**(60 volunteers): control, i.e. Rabies vaccine 1ml followed by Rabies vaccine 1ml 8 weeks later.

Oral antimalarials will be taken by all participants from days 63-65 inclusive. The purpose is to clear any asymptomatic parasitaemia (both asexual blood stage parasites and gametocytes) prior to the commencement of PCR monitoring for new malaria infection from Day 70. A standard 3 day course of Atovaquone/proguanil will be combined with three days of concurrent oral artesunate. Atovaquone/proguanil has been chosen over artemether/lumefantrine to limit the potential for persistence of antimalarial drug from Day 70 when monitoring for new malaria infection commences (lumefantrine has a relatively long elimination half life). Artesunate has been selected because of its antigametocidal activity. The anti- malarial treatment will be directly observed.

The control group will undergo similar tests to the vaccinated groups (such as ex-vivo and cultured ELISPOT and ICS) to control for T cell responses to TRAP and other antigens which may develop during the study period as a result of natural exposure to *P. falciparum*.

All volunteers will follow the same schedule for clinic visits and field worker visits, vaccinations (Rabies vaccine or ChAd63 ME-TRAP / MVA ME-TRAP, depending on group), antimalarial treatment, and intensive PCR monitoring. There will be a total of 24 clinic attendances, 22 blood

sampling occasions (including finger-prick samples), 2 field workers home visits and two vaccination visits for each volunteer.

### **Selection and withdrawal of subjects**

We will continue to recruit and screen volunteers until at least 120 eligible volunteers have been identified, preferably until 130 eligible volunteers have been identified. If volunteers withdraw consent prior to receiving their first vaccination, we will screen and recruit in order to replace the number withdrawing consent.

#### ***Inclusion Criteria***

- Consenting adult males aged 18 – 50 years in good health.
- Will remain resident in the study area for the study duration.
- Able and willing (in the Investigator's opinion) to comply with all study requirements
- Informed Consent

#### ***Exclusion criteria***

Any of the following constitutes exclusion criterion:

- Any significant medical disease, disorder or finding which may significantly increase the risk to the volunteer because of participation in the study, affect the ability of the volunteer to participate in the study or impair interpretation of the study data
- Hypersensitivity to Rabies vaccine, the trial vaccines or the antimalarial used.
- History of allergic disease or reactions likely to be exacerbated by any component of the vaccines, e.g. egg products, kathon, neomycin
- History of splenectomy.
- Haemoglobin less than 10.0 g/dl
- Clinically significant abnormalities of laboratory screening tests (full blood count, ALT, creatinine levels).
- Blood transfusion within the month preceding enrolment.
- History of vaccination with previous experimental malaria vaccines or other vaccines likely to impact on findings of study (e.g. other MVA or adenovirus vectored vaccines)
- Administration of any other vaccine or immunoglobulin within 2 weeks before vaccination.
- HIV or Hepatitis B surface antigen seropositivity.

- Current participation in another clinical trial or recent participation within 12 weeks of this study.
- Any other finding which in the opinion of the investigators would increase the risk of an adverse outcome from participation in the trial.
- Likelihood of travel away from the study area

### ***Withdrawal criteria***

Subjects may be withdrawn from the study:

- By withdrawing consent
- On the decision of the investigator
- On the advice of the data safety and monitoring board (DSMB)

The investigator may withdraw the subject for the following reasons:

- Any adverse event which results in the inability to comply with study procedures
- Ineligibility either arising during the study or retrospectively (having been overlooked during screening)
- Significant protocol deviation.
- Loss to follow up (applies to a subject who consistently does not return for protocol study visits, is not reachable by telephone or any other means of communication and/ is not able to be located).

The reason for withdrawal will be recorded in the case report form (CRF).

If a subject is withdrawn for any reason, the reason will be recorded. If withdrawal is the result of a serious AE, the investigator will offer to arrange for appropriate specialist management of the problem and the ethical committee will be informed in a timely manner. The extent of follow up will be determined by a medically qualified investigator, but will be at least for the whole study period. Subjects withdrawn prematurely for any reason will not receive further vaccinations, although they may be requested to come back to the clinic for safety evaluation.

### **Study schedule and procedures**

#### **Screening visit**

Volunteers will be provided with detailed information about the study, as described in the attached information sheet. Consent will be written. After informed consent has been obtained the study clinicians will take a clinical history, examine all volunteers carefully and conduct a number of standard laboratory tests (FBC, ALT, rapid HIV tests, creatinine and Hepatitis B surface antigen test) to screen subjects for clinically significant acute or chronic illnesses. Those with abnormal results will be offered appropriate investigations and treatment or referral as

necessary. A photograph will also be taken in order to produce a study identification card which will be given to the volunteer. The electronic stored version of the photograph will be identified by the unique study number only and destroyed at the end of the study.

### **HIV testing**

Volunteers will have access to a trained counsellor who will do pre and post test counselling. HIV sero-status will be established using the standard rapid diagnostic kits and testing algorithm used by the Senegalese Ministry of Health and Prevention. Those diagnosed positive will be referred to the HIV Department of King Baudouin hospital for further counselling and treatment.

### **Enrolment**

Volunteers are considered enrolled into the study when they receive their first vaccination. This should occur  $\leq 90$  days after the screening visit. They will remain in the vaccinating health facility for 30 minutes post vaccination in order to enable monitoring by the study clinicians. The vaccination health facility will have resuscitation equipment and drugs available during vaccination clinics. The study clinicians will assess and record local as well as systemic adverse events after 30 minutes have elapsed.

### **Follow- up**

Participants will be followed up for approximately 6 months after the first vaccination. Study clinicians and field workers supervised by medical officers will assess and record local adverse events post vaccination including pain, swelling and discolouration. He or she will then assess and record systemic adverse events including temperature, malaise and nausea. Each side effect will be classified as absent, mild, moderate or severe. Each volunteer will be seen 2 weeks after ChAd63 ME-TRAP vaccination and 1 week after MVA ME-TRAP vaccination for a full safety and reactogenicity assessment by a study clinician. An additional visit at home will be made by a field worker (reporting to the study clinicians) on day 1 after each vaccination, and if necessary daily as directed by a study clinician. The study clinicians will review reports from home visits conducted by field workers, and arrange to see the volunteers in person if appropriate.

The volunteers will be asked to present themselves to the study Hospital if they develop any illnesses during follow up. Any emerging safety data that is considered cause for concern by the DSMB will be relayed to the participants during the study visits.

**Table 1: Solicited local and general adverse events to be documented in the CRF**

| Adverse events         |                                                   |
|-------------------------------|---------------------------------------------------|
| Local (injection site) | Pain at the injection site                        |
|                               | Redness at the injection site                     |
|                               | Swelling at injection site                        |
|                               | Warmth at the injection site                      |
| General                | Documented fever (axillary temperature > 37.5° C) |
|                               | Symptoms of feverishness                          |
|                               | Malaise                                           |
|                               | Arthralgia                                        |
|                               | Headache                                          |
|                               | Myalgia                                           |
|                               | Nausea / vomiting                                 |
|                               | Other(specify)                                    |

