### **What risks may be involved?**

The general risks to participants are those associated with blood sampling and vaccination. Mild local tenderness and bruising, light-headedness, or rarely vasovagal syncope, may result from venepuncture. As with any invasive procedure, infection is also a risk. This risk is minimized by the use of pre-packaged sterile equipment and careful attention to proper technique. There is no risk of HIV infection from phlebotomy since all needles are disposed of after a single use. While performing the procedure, loss of vacuum or collapsed vein might necessitate another draw.

Potential risks from vaccination include local and systemic reactions, which shall be solicited for in this study. Local symptoms including discomfort/pain, redness, swelling, and tenderness at the site of injection may be experienced by the volunteers. Systemic symptoms including myalgia, arthralgia, fatigue, malaise, headache, nausea, vomiting, fever or feverishness may be experienced by the volunteers.

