### **ChAd63 ME-TRAP**

To date, 186 volunteers have received ChAd63 ME-TRAP. Local adverse events such as pain would be expected to occur frequently. Less frequent local adverse events are likely to include erythema, swelling and warmth. Local adverse events are likely to be mild in nature and should resolve rapidly. Common systemic adverse events post viral vectored vaccines include headache, feverishness, myalgia, arthralgia, fatigue and malaise. Generally volunteers report a transient flu like illness within 24 hours of vaccination with ChAd63 which resolves completely within 48hrs. It is anticipated that the majority of systemic adverse events post ChAd63 ME-TRAP will be mild in intensity. No vaccine related serious adverse events have been seen with ChAd63 ME-TRAP.

During the manufacturing process of ChAd63 CS, a biocide named Kathon is used. Kathon is added to body washes, conditioners, liquid soaps, shampoos and wipes as a preservative. The

maximum dose is 0.1% for 'rinse off' products and for 'leave on' products it is 0.05%. It has been approved by regulatory authorities throughout the world as a preservative in these products. As a skin sensitiser it is known to cause contact dermatitis. An internal study was set up to look at the levels of Kathon that were removed during the final purification step of buffer exchange. This study utilized high performance liquid chromatography and showed that trace amounts of Kathon may be left on the column after carrying out the rinse and sanitisation steps. However, the study confirmed greater than 99.9975% removal of Kathon to approximately 30 fold less than the limits for 'leave on' products containing Kathon. We will exclude anyone from the study with a history of clinically significant contact dermatitis or sensitivity to Kathon.

There are no additional safety concerns arising from clinical trial experience with the administration repeated doses of ChAd63 ME-TRAP. As described in the Investigator Brochure for ChAd63 ME-TRAP, five volunteers have received a second dose of ChAd63 ME-TRAP after vaccination with ChAd63 ME-TRAP followed by MVA ME-TRAP (VAC033 clinical trial, completed). In the ongoing VAC043 clinical trial, 12 volunteers have received two sequential doses of ChAd63 ME-TRAP and a further 6 have received three sequential doses.

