### **MVA ME-TRAP**

More than 700 volunteers have received MVA ME-TRAP in the United Kingdom (UK), Senegal and the Gambia. Most volunteers developed erythema (or discolouration in African skin) and swelling post vaccination which in the majority of cases was mild to moderate in nature. This was accompanied by discomfort, warmth, itching and scaling which typically resolved to a faint flat papule. Intramuscular administration of MVA ME-TRAP has significantly less local reactogenicity than intradermal. Local AEs are likely to be mild in nature and should resolve rapidly, although there is the possibility of moderate arm pain in some cases. Common systemic adverse events post MVA vectored vaccines include headache, feverishness, myalgia, arthralgia, fatigue, and malaise. Generally volunteers report a transient flu like illness within 24 hours of vaccination with MVA which resolves completely. It is anticipated that the majority of systemic adverse events post MVA ME-TRAP will be mild or moderate in intensity. No vaccine related serious adverse events have been seen with MVA ME-TRAP.

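### Table 1 has no row for fatigue and names only redness, while other sections call fatigue common and tell staff to record discolouration; the lists should be reconciled

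*Protocol*

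**What the plan says.** Table 1 in Section 9 is titled "Solicited local and general adverse events to be documented in the CRF". It has four local rows (pain, redness, swelling, warmth) and seven named general rows (documented fever, feverishness, malaise, arthralgia, headache, myalgia, nausea/vomiting), plus a free-text row for anything else. The only row on skin colour is "Redness at the injection site".

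The Follow-up text immediately before the table uses another term. Staff are to record "local adverse events post vaccination including pain, swelling and discolouration", and each side effect is to be classed as absent, mild, moderate or severe.

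Section 10, Collection of Adverse events, has the largest diameter of redness and of swelling measured in millimetres. The grading tables that follow cover swelling (a) and redness (b); there is none for discolouration.

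In Section 15, What risks may be involved?, the protocol says: "Potential risks from vaccination include local and systemic reactions, which shall be solicited for in this study". Two sentences later: "Systemic symptoms including myalgia, arthralgia, fatigue, malaise, headache, nausea, vomiting, fever or feverishness may be experienced by the volunteers". For the priming vector: "Common systemic adverse events post viral vectored vaccines include headache, feverishness, myalgia, arthralgia, fatigue and malaise". The MVA ME-TRAP text gives the same six reactions as common and, on the skin, reports: "Most volunteers developed erythema (or discolouration in African skin) and swelling post vaccination".

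**The concern.** Safety and reactogenicity form a secondary objective (Section 8), and Section 13, Safety data, compares the control and malaria vaccine regimens on reactogenicity. That comparison is cleanest when every expected reaction is asked for by name and graded on one scale in every participant. Here two reactions that the protocol itself expects from the vectors fall outside the named list or the graded scale, in a trial whose participants are adult men in Senegal.

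If staff work from Table 1, nobody is told to ask about fatigue, and a clinician who sees discolouration must decide whether it counts as redness. Section 9, Study groups, blinds volunteers, field workers and laboratory scientists but not the clinical investigators, and Section 10 has the investigator assess severity and relationship. Part of the discretion left by the conflicting terms therefore sits with people who know the allocation.

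**Working it through.** The protocol gives no figure to reproduce and no arithmetic beyond counting applies. The check sets the lists side by side.

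**Systemic reactions**

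| Named in Section 15 (general risks) | Called common for both vectors | Named row in Table 1 |
|---|---|---|
| Headache | yes | yes |
| Fever or feverishness | yes (feverishness) | yes (two rows) |
| Myalgia | yes | yes |
| Arthralgia | yes | yes |
| Malaise | yes | yes |
| Fatigue | yes | **no** |
| Nausea, vomiting | not in that list | yes (one row) |

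Fatigue is the only systemic symptom in the general-risk paragraph without a row. Of the six called common after both vectors, five have a row: 6 − 5 = 1 missing. All three Section 15 lists name fatigue and malaise separately, so on the protocol's own usage the malaise row does not stand in for fatigue.

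**Local signs**

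| Named under Follow-up | Named row in Table 1 | Scale in Section 10 |
|---|---|---|
| Pain | yes | yes (Table 5) |
| Swelling | yes | yes (grading a) |
| Discolouration | **no** (redness instead) | **no** (grading b is for redness) |

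One of the three signs that Follow-up requires has neither a row nor a specific scale.

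**Other routes of capture**

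1. Follow-up itself requires discolouration to be recorded and gives it a four-level severity class.
2. Table 1 has a free-text row in its general part.
3. Section 10 has participants asked at each visit about side effects since they were last seen.
4. Section 10 also has unsolicited events documented, and the safety endpoint in Section 9, Secondary Endpoints, covers solicited and unsolicited events alike.

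So fatigue lacks only its own prompt, and discolouration lacks a row and a millimetre grade. Neither is left without any means of being recorded.

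**Timing.** The ChAd63 ME-TRAP risk text describes a flu-like illness that begins within 24 hours and is gone within 48. The scheduled contacts after that dose are the field worker's visit on day 1 and the clinic visit on day 14 (±7 days). The day 1 visit is therefore where a named prompt for fatigue would help most; by day 14 the answer depends on recall.

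**The case against.** The strongest reply is that this is a difference of terms and not a gap in collection. Discolouration is explicitly to be recorded and classed by severity. The MVA ME-TRAP text treats erythema and discolouration as one reaction seen in different skin, so the redness row can be read to include both. Participants are actively questioned at each visit, so the free-text row does not depend on wholly spontaneous reports. The sentence on soliciting refers to local and systemic reactions in general; fatigue comes later, among symptoms that may occur. Section 15 is a risk statement, not an assessment schedule, and its general list also says redness. The form and diary card are not shown.

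Most of this stands, and it removes the stronger readings. A reader might infer that the reactogenicity objective misses these reactions; the four routes above show that it does not. A reader might also infer that the malaria regimen would look less reactogenic than it is. The protocol does not support that either: both arms use the same list, the rabies vaccine text also reports redness among its local reactions (21–74% of vaccinees), and no fatigue rate is given for either arm. Nor can the report that most MVA ME-TRAP recipients had a skin reaction be carried over directly. It concerns that vector only, and the same text says that the intramuscular route, the only one used here, gives significantly less local reactogenicity than the intradermal. For ChAd63 ME-TRAP, erythema is among the less frequent local events.

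What survives is narrower. No instruction tells staff to enter discolouration as redness, the two adjacent parts of Section 9 use different terms for the same assessment, and a general question about side effects is not the same as a named prompt.

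**Conclusion.** The inconsistency is real and minor. One of six systemic reactions called common has no prompt in the solicited list, and one of three local signs required under Follow-up has no row and no millimetre grade. Recording of both may vary between assessors and visits, and some under-recording is possible. Its size, and whether it would differ between arms, cannot be determined from the protocol.

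The conclusion assumes that the case report form and diary card follow Table 1 as printed. If they already prompt for fatigue and discolouration, only the protocol wording needs correcting. The primary endpoint, the sample size and the reporting of serious adverse events are not touched. The change is worth making because it is nearly free and improves the data for a stated secondary objective.

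**What to change.** Reconcile the following into one list of solicited terms with matching scales: Section 9 (Follow-up and Table 1), Section 10 (Collection of Adverse events and grading table b) and Section 15 (the general, ChAd63 ME-TRAP and MVA ME-TRAP risk texts).

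- In Table 1, add *Fatigue* under the general events.
- In Table 1, replace the redness row with *Redness or discolouration at the injection site*.
- In Section 10, have the largest diameter of redness or discolouration measured, and retitle grading table b to match.
- Use the same combined term under Follow-up and in the risk texts.

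The cost is a small edit to the case report form and diary card, with no added visits, staff or blood samples. The drawback is slightly less comparability with trials that recorded erythema only. The edit should be in place before the first vaccination, because symptoms not asked about at the time cannot be recovered reliably afterwards.
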